**Figure 4. f4:**
[figure not shown]
Study recruitment summary flowchart (see supplementary documents for detailed flowcharts).

### Longitudinal cohort and weekly stool sampling

A subset of children will continue to have extra follow-up visits with blood samples at six, nine and 12 months to track individual immunity and waning over time. In addition, this subset will have additional monthly stool samples and malaria RDTs to explore the extent of missing exposures which may have an impact less than three months on humoral immunity, and the impact of repeated exposures on acquisition of immunity. We will carry out weekly follow-ups for a subset of children with
*Salmonella* stool culture up until they have two consecutive negative stool cultures, to assess the duration of asymptomatic
*Salmonella* carriage.

**
*Case-control study*
**

We will prospectively recruit any child between the ages of 0–5 years with a positive blood culture for NTS at Queen Elizabeth Central Hospital (QECH), Zingwangwa and Ndirande health centres. Participants will have a blood sample to test for immune markers as close as possible to presentation, as soon as blood culture is determined to be positive, and repeat samples at one, three-, six-, nine- and 12-month follow-ups. These samples will be tested for antibody and bactericidal activity to NTS and other immune markers to understand acquisition of immunity post-invasive disease compared to immunity developed in the community sero-survey data. All other details including risk factor testing and socio-economic and WASH questionnaires will be carried out in the same way as the main study. For each case, a control from the community serological survey data from SAiNTS samples will be recruited and matched on age and geographic location (as close as possible) to compare immune markers at baseline and post-invasive disease to help validate estimated correlates of protection.

Blood culture positive cases of
*Salmonella* Typhi will also be recruited and have a blood sample taken at presentation at one, three, six, nine and 12 months to measure antibody kinetics for immune markers for acute typhoid infection, to inform models to estimate seroincidence of typhoid infections from future community serosurveys. Stool samples will also be collected at each visit. The stool will be tested for
*Salmonella* and
*E. coli* and other microbes associated with health and disease which can be found normally in healthy children and to look at the health of the gut. Additionally, information on antibiotic usage in the past month will be collected from both the confirmed blood culture case and members of their household.

**
*Serosurveys in other sub-Saharan African sites*
**

As part of the VacciNTS sero-epidemiology work-package three other field (Kenya, Burkina Faso and Ghana) sites have been chosen for the sero-epidemiological surveys. A core protocol has been written for all sites (see Vacc-iNTS Core protocol for details of study methodology for other sites (
*Extended data*
^
6
^)). Malawi will be the central site for this project, leading on data management and laboratory training for other sites – with support from GVGH. A minimum of 1000 children will be recruited from each of the 4 sites (Malawi, Kenya, Burkina Faso and Ghana). In Malawi we have planned to expand the sample size to 2500 and to take paired samples 3 months apart with additional meta-data on iNTS risk factors. The other sites will not test for risk factors, or use RTS,S/AS01 vaccine study sites. All serological samples will be tested for IgG and SBA for NTS, however, there is no obligation for the other sites to test for risk factors.

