**Exploratory objectives**

1.   To define an antibody CoP based on the inverse relationship between known age-stratified clinical disease incidence and age-stratified seroprevalence.

2.   To investigate the impact of malaria (RTS,S/ AS01) vaccination on age-stratified acquisition of bactericidal activity against NTS.

3.   To investigate how intestinal inflammation/ environmental enteropathy relates to enteric NTS infections and development of immunity.

4.   Understand antibody kinetics of immune response to NTS and
*Salmonella* Typhi in blood culture confirmed cases and community serosurvey samples to inform seroincidence estimates.

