Detailed immune and antigenic investigation of these samples will be carried out in collaboration with OptiVaNTS. An immune correlate of protection will be estimated using age-stratified acquisition of immunity and age-stratified incidence of clinical disease defined by routine blood cultures collected through MLW-Queen Elizabeth Central Hospital. Stool samples will be tested for salmonella culture and Polymerase Chain Reaction (PCR), which will enable us to model the effect of eNTS at visit 1 to induce systemic immunity at visit 2. Data will be collected on sociodemographics and indicators of water, sanitation and hygiene (WASH) using the REDCap and Open Data Kit (ODK) platforms (see
Table 1).

**Table 1. T1:** Summary of data to be collected.

Biological measure	Variable	Target n observations	Methods
Enteric Salmonella infections (usually transient & asymptomatic)	eNTS event	4000	Stool culture in selective broth, DNA extraction and qPCR for TTR gene.
Serological marker of invasive NTS infection	iNTS event	4000	ELISA for anti-S. Typhimurium and S. Enteritidis LPS IgG, conducted on 3-month paired serum samples.
Functional protective measure of serum killing	Serum killing	4000	Serum bactericidal activity high-throughput assay conducted on 3-month paired serum samples.
Rainfall and temperature	Climate	475 days	Daily measurements by Malawi Meteorological Office.
Poverty and sanitation	Poverty	4000	Validate questionnaire of household wealth and WASH (water, sanitation, and hygiene).
Current or recent malaria	MRDT	4000	Point-of-care fingerprick lateral flow antigen detection Malaria Rapid Diagnostic Test (P. falciparum HRP2 detection).
Haemoglobin	Hgb	4000	Haemoglobin (g/dl) measured by point of care fingerprick haemocue test.

We will compare the age-stratified acquisition of immunity (IgG and SBA) between children receiving the malaria vaccine (RTS,S/AS01) and un-vaccinated children matched on factors known to influence vaccine uptake. The EPI-MAL study has conducted a GPS-mapped household census, allowing us to randomly select children across the study age-strata to approach for recruitment. Selection of enumeration areas has assumed approximately 50% uptake of consent to the study, and statistical power calculations have assumed a further 10% drop out for the second visit.

Detailed schemas illustrating the rotation of field teams recruitment and sampling of stool and blood are shown in
Table 2 &
Figure 4 also see
full protocol (
*Extended data*)
^
6
^.

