### Sample storage and analysis

All laboratory process have specific SOPs which are stored in the OSF folder (
https://doi.org/10.17605/OSF.IO/FUE3T
^
6
^).

**
*Serum sample collection and processing*
**

Serum samples were collected in serum-gel vacutainers and transported daily to the main laboratory at KUHeS in Blantyre in cooler boxes with temperature loggers, maintaining a temperature of 4–8°C. Subsequently, the samples were centrifuged, aliquoted and stored at -70°C (range -65°C to -80°C).

**
*Analysis of clinical sera by ELISA*
**

Assays developed by our collaborators at GVGH will be performed as per published protocols by
Aruta
*et al.*, 2023. Briefly, antibody titers to OAg from S. Typhimurium and
*S.* Enteritidis in samples from all subjects at each time point will be analysed. Test samples, in triplicate, will be analysed at three dilutions (1:100, 1:4000, 1:160,000), and colour change compared with a standard curve made with calibrated human serum pool included on each assay plate. This pooled serum pool will be collected from high-titre adult donors in Malawi, identified from the STRATAA study (Meiring 2019) validated as the serum standard at GVGH and used across the four sub-Saharan African sites. The anti-O-Ag IgG concentration to S. Typhimurium and S. Enteriditis, in the serum standard was determined at GVGH. Anti-OAg responses will be expressed in ELISA units (EU)/ml. Test sample ELISA units are interpolated from the standard curve. Well-characterized standard OAg from
*S.* Typhimurium and
*S.* Enteritidis will be used as plate coating antigen. Positive and negative controls are created from the serum standard at set concentrations of 1.41 and 0.69 EU/ml respectively. Standard curves for each plate were assessed by a number of parameters including a minimum r-squared value, minimum (0.5) and maximum (2) optical density readings at 1 EU/ml, and maximum 20% error from expected concentration values from back-calculations (Aruta
*et al.*, 2023). BioTek™ 50TS Microplate Washer and BioTek™ 800TS Absorbance Reader will be used for the ELISAs.

**
*Analysis of clinical sera by SBA*
**

Serum Bactericidal Activity will be measured using a high-throughput fluorescent assay, which detects bacterial ATP as a readout of viability, developed by members of the VacciNTS consortium
^
19

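### The case baseline sample is an acute, post-onset sample, yet it is compared with community controls to help validate correlates of protection, without adjustment or caveat

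*Protocol article*

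**What the plan says.** All references are to the protocol article.

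- **Timing.** Under *Case-control study*, children enter as cases after a positive culture for non-typhoidal *Salmonella*. The first immune sample is taken "as close as possible to presentation, as soon as blood culture is determined to be positive", with repeats at one, three, six, nine and 12 months. No pre-illness serum from cases is described.
- **Use.** Each case is matched on age and location to a child from the community survey "to compare immune markers at baseline and post-invasive disease to help validate estimated correlates of protection". The same section gives another purpose for the case samples: "to understand acquisition of immunity post-invasive disease compared to immunity developed in the community sero-survey data".
- **Correlate.** Exploratory objective 1 is "To define an antibody CoP based on the inverse relationship between known age-stratified clinical disease incidence and age-stratified seroprevalence".
- **Markers and infection.** Table 1 lists anti-LPS IgG under "Serological marker of invasive NTS infection". Exploratory objective 4, which begins "Understand antibody kinetics of immune response to NTS and", covers blood-culture-confirmed cases.
- **Assay.** The SBA section describes a method "which detects bacterial ATP as a readout of viability", run with added baby rabbit complement. It gives an IC50 range for the serum standard and refers to a publication for further plate checks. *Sample storage and analysis* says that all laboratory procedures are held in the extended data.
- **Antibiotics.** The article says that "information on antibiotic usage in the past month will be collected from both the confirmed blood culture case and members of their household". It does not relate that use to the time of the serum draw.

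**The concern.** A correlate of protection, as the article defines it in its introduction, is a marker statistically linked to a reduced risk of disease. Evidence for one should come from immunity as it stood before the illness. The first case sample cannot supply that directly, because it follows both disease onset and culture turnaround. The plan nevertheless sets baseline against post-invasive disease as if the first were free of the infection.

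Two distortions are possible. The infection may have raised or lowered antibody and SBA before the draw. Separately, an assay that reads viability may count inhibition of the test strain by antibiotic in the serum as serum killing.

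At stake is how the case-control contrast is read. A real deficit in susceptible children could be hidden. Equally, a difference that the illness produced could be taken as support for a protective threshold. Recruiting more cases would not help, because this is bias and not imprecision.

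**Working it through.** **1. Passages side by side**

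- The sampling rule places every first case serum after onset. The stated comparison calls that value baseline and uses it as evidence on protection.
- Table 1 ties anti-LPS IgG to an invasive event, and exploratory objective 4 expects antibody to move over time in cases. On the article's own premises, the acute value need not equal the pre-disease value.
- *Description of statistical methods* includes no term for time since onset or since culture draw.
- A record of antibiotic use in the past month cannot separate a course that ended weeks earlier from drug present at the draw.

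**2. The plan's own figure**

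*Change in SBA in longitudinal cohorts* states power over 80% with 20 per arm for an SBA difference of 0.75. It gives no SD, within-child correlation or significance level, so the figure cannot be strictly reproduced. I assumed two-sided 0.05, independent arms and a single comparison:

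power = Φ( d / (SD·√(2/n)) − 1.96 ), with n = 20

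- SD 0.4, borrowed from the enteric-exposure calculation: SE = 0.4 × √0.1 = 0.1265; 0.75/0.1265 − 1.96 = 3.97; power 99.99%. Only 5 per arm would be needed for 80%.
- SD 0.83, chosen because it gives roughly the stated power: SE = 0.83 × √0.1 = 0.2625; 0.75/0.2625 − 1.96 = 0.90; power 81.5%.

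The statement of over 80% holds in both cases. The concern does not depend on it.

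**3. Sensitivity to a shift in case values**

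Let b be an assumed shift in case SBA between the pre-disease state and the draw. The documents give no value for b and no sign for the 0.75. If cases truly lie 0.75 below controls and b is upward, the apparent difference is 0.75 − b:

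| b | Apparent difference | Power, SD 0.4 | Power, SD 0.83 |
|---|---|---|---|
| 0 | 0.75 | >99.9% | 81.5% |
| 0.25 | 0.50 | 97.7% | 47.8% |
| 0.375 | 0.375 | 84.2% | 29.8% |
| 0.50 | 0.25 | 50.7% | 15.7% |
| 0.75 | 0 | 2.5% | 2.5% |

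The last row is the rejection probability in the expected direction when no contrast is left.

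The same formula covers a downward shift. If there were no true pre-disease difference and illness lowered case values by 0.375, the apparent deficit would be 0.375. A deficit would then be declared with probability 84.2% (SD 0.4) or 29.8% (SD 0.83). The error can therefore run either way.

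These figures are illustrations only. The 0.75 is given for a comparison over several visits, not for the acute sample alone, and the calculation ignores matching and repeated measures.

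**The case against.** The strongest reply is that a case cannot be known before the culture is positive, and the article already asks for the earliest sample after that. This is true, so the timing itself is not the fault. What needs correcting is the label and the use made of the sample.

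Second, the correlate does not rest on case titres. It is an exploratory, population-level estimate from age-specific incidence and immunity, and the article says only that the comparison will help validate it. This stands. A reader might infer that the comparison cannot validate anything; the documents do not support that.

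Third, a reader might infer that cases have usually received antibiotics before the draw, that only cases are affected, or that controls are afebrile. None of this is stated. The article records antibiotic use without its timing. The community cohort excludes only non-residents and children judged clinically unstable, and it enrols children with malaria. Antibiotic in case sera is a possibility, not an established fact.

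Fourth, the cited assay publication and the laboratory procedures are not shown. They may already include a control for killing without complement, so its absence from the article is not a finding.

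Fifth, the net direction is open. An early antibody response would raise case values. Consumption of antibody, or the impairment of humoral defence that the article attributes to current or recent malaria, could lower them. Added complement removes one acute-phase distortion of SBA, but not a change in antibody and not an inhibitor in the serum.

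**Conclusion.** The point holds in limited form. The article fixes when the first case sample is drawn and how it will be used, and the two do not fit: a post-onset value is compared with community values as baseline evidence on protection, without adjustment or caveat.

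The size and direction of the resulting bias cannot be derived from the documents. The range in the working rests on an assumed shift, an assumed significance level and two assumed SDs. It shows only that a shift of half the planning difference could matter, and would matter much more at the larger SD. The antibiotic mechanism is plausible because the assay reads viability, but its frequency is unknown and it may already be controlled.

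The consequence is confined to a supporting check on an exploratory objective. The main route to the correlate does not use case titres, and the aim of describing immunity after invasive disease is unaffected, since it needs post-onset samples.

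**What to change.** 1. Call the first case sample acute or enrolment instead of baseline.
2. Record days from symptom onset to serum, days from culture draw to serum, and whether antibiotics were given before the serum draw.
3. Adjust or stratify the acute case-control contrast by that time. Controls have no time since onset, so a practical form is to analyse the difference within each matched pair against the case's delay. Extrapolating to day zero should not be presented as pre-disease immunity.
4. Unless the laboratory procedures already do so, run acute case sera with a control containing no active complement, for both test strains. In the SBA contrast, exclude sera that kill without complement, or handle them in a sensitivity analysis. Choose between these before seeing results.
5. State that acute IgG and acute SBA are both supportive only for the correlate. IgG should not be ranked as the main marker: it avoids the antibiotic artefact, but it is the marker Table 1 ties to the invasive event.

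The cost is two or three data fields, a few control wells and some acute SBA values lost. On the power statement's 20 cases and two strains, the controls come to 20 × 2 = 40 serum-strain combinations before replicates; 20 is not a stated recruitment target, so the number may differ. Patient care and the visit schedule do not change. The timing fields should be in place before recruitment where possible, since they may be hard to recover later.

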### Study population

**
*Prospective community cohort and longitudinal cohort*
**

Guardians of children aged 0–5 years resident in Chikwawa district enumeration areas defined by the EPI-MAL trial will be approached to enter the study.

**Inclusion criteria**

-   Child ≤ 5 years

-   Planning to be in study area for next three months

**Exclusion criteria**

-   Not resident in the catchment area

-   Deemed clinically unstable by the survey team

**
*Case control study*
**

We will prospectively recruit any child between the ages of 0–5 years with a positive blood or cerebrospinal fluid culture for NTS identified through the Malawi Liverpool Wellcome (MLW) Programme’s Laboratory Information Management System (LIMS) as a case.

**Inclusion criteria (iNTS Cases)**

-   Blood or cerebrospinal fluid culture positive for non-typhoidal salmonella

-   Child ≤ 5 years

### Study period

The study is planned to be carried out over three years from proposal to dissemination of findings (see Gantt chart [
Table 3] outlines the timing of planned study activity and quarter of completion.

**Table 3. T3:** Gantt chart of planned study activities.

Activity	2020						2021												2022												2023					
Year and Quarter	Q3			Q4			Q1			Q2			Q3			Q4			Q1			Q2			Q3			Q4			Q1			Q2		
Rainy season																																				
NTS peak-season																																				
Ethics & governance																																				
SOP’s, data tools & validation																																				
Public & community engagement																																				
Stakeholder engagement																																				
Fieldwork test-pilot																																				
Field sampling cohort 1																																				
Field sampling cohort 1&2																																				
Field sampling cohort 2&3																																				
Field sampling cohort 3&4																																				
Field sampling cohort 4																																				
Lab analyses in real-time																																				
Lab analyses 4000 stored samples																																				
Data cleaning																																				
Primary Mathematical modelling																																				
Secondary Mathematical modelling																																				
Analysis across all VacciNTS sites																																				
Data write-up, presentation																																				
Feedback to community & stakeholders																																				

### Sample size

 All code can be found
here (
*Extended data*
^
18
^).

**
*Sample size simulations for serosurvey*
**

Simulated data (100,000 simulations) demonstrate an acceptable margin of error and confidence interval for estimation across all seroprevalences for 1000 single samples (200 in each of five age groups, from 0–11, 12–23, 24–35, 36–47, 48–60 months), as a minimum sample size for each site in Malawi, Kenya, Burkina Faso, and Ghana (
Figure 5).

**Figure 5. f5:**
[figure not shown]
Margin of error and 95% Confidence Intervals across the range of seroprevalences.

**
*Sample size simulations for community cohort (Malawi site only – additional analysis)*
**

Power for detecting change in seroconversion rates due to enteric salmonella exposure eNTS.

Power was estimated for the change in seroconversion comparing proportions of unequal size between two groups (visit 1 and visit 2). A range of scenarios are computed around the initial proportion of individuals that are already seroconverted at the first sample and how many more are seroconverted at the second sample. Power is high for most scenarios, particularly when the effect of exposure results in a doubling or more of the seroconversion rate (
Figure 6A).

**Figure 6. f6:**
[figure not shown]
**A**: Power for detecting seroconversion following enteric infection.
**B**: Power for detecting change in SBA following enteric salmonella exposure (8%) prevalence (N=2500).

**Change in SBA due to eNTS**

Statistical power is high across a range of assumptions (
Figure 6B). With a sample size of 2,500 recruited individuals, 20% loss to follow-up, a difference of 0.2 in SBA between children with salmonella PCR-positive stools compared to those with negative stools, can be detected in the three-month follow-up visit sample with 99.97% power, assuming a standard deviation of 0.4 for SBA (
Figure 6B).

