**Changes in antibody titer by age**

 There is good power (>80%) to detect a difference of 13 antibody titer between visits for children with and without either malaria or anaemia with a sample size of 2500 (
Figure 7A–C). For malnutrition and sickle cell disease the changes in antibody titre between samples has good power (>80%) to detect a change in antibody titre of 47 and 68 respectively between visits for a sample size of 2500, which is much less sensitive than the other methods – therefore these will be exploratory endpoints (
Table 4).

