**Figure 7. f7:**
[figure not shown]
**A**: Power for detecting change in SBA due to malaria infection.
**B**: Example of data from a single simulation (malaria).
**C**: Power curves for detecting impact of anaemia on mean NTS antibody level.

**Table 4. T4:** Summary of all sample size calculations carried out by risk factor and outcome.

Risk factor	Prevalence	Difference in SBA between 3 monthly samples (CFU/ml)	Difference in antibody titer	Difference in seroconversion over 3 months	Power to detect effect
*Malaria*	16%	0.25	13		>=80%
*Moderate to severe anaemia*	20%	0.225	13		>=80%
*Malnutrition*	2%	0.65	47		>=80%
*Sickle cell disease*	1%	0.9	68		>=80%
*Enteric NTS infection*	8%	0.2	15	15–20%	>=80%/ 99.97%
*Malaria RTS,S/AS01 vaccination*	60% coverage	1.5	-	-	>=80%

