**Changes in serum bactericidal activity by age**

With malaria prevalence of 16%, the simulations found that 2,500 paired samples would be well-powered (power >80%) to detect changes in SBA of 0.25 CFU/ml between three-monthly samples (
Figure 8A–B,
Table 4). This change is equivalent to the gain in SBA activity naturally acquired over 2.5 months in the 9-36-month age-group, therefore lower than would be expected to be seen over a three-month period on average of natural acquisition of immunity. Simulations were run for other risk factors and protective factors including malaria vaccination (
Table 4 and
Figures 8C and 8D).

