^. The assay will be conducted in the presence of full complement repletion with 50% baby rabbit complement. Results will be available on the same day, without the need for overnight incubation or colony counting. The samples from all subjects will be analysed, in triplicate, by SBA assay using
*S.* Typhimurium and
*S.* Enteritidis wild type strains. Well-characterized cell banks of the test strains will be routinely used for the SBA. The serum standard will be tested on each plate; IC50 of the standard should be in the target range of 3x10
^3^ and 3x10
^4^. Validation checks for plates to pass quality control are outlined in [
Aruta
*et al*., 2022]. BioTek™ Synergy™ HTX Multi-Mode Microplate Reader will be used for luminescence readings.

All serological laboratory assays (ELISA and SBA) will be standardised throughout the consortium, and quality assurance between sites will be conducted, with the aim of becoming the international standard assays for use in future iNTS clinical trials, thus ensuring highly comparable dataset for modelling approaches across the consortium. Standardized sera has been validated between Malawi and GVGH to ensure reproducibility of both assays. Malawi is the African reference site for the assay. A detailed description of this SBA method has recently been published by
Aruta
*et al.,* 2022. All sample analysis will be done in Malawi for all sites, including assay transfer of the ELISA and L-SBA assays. The Ghana site will also transfer the assays to their site and will be cross-validated in Malawi.

**
*Processing and analysis of stool samples*
**

Briefly, stool samples will be collected in the field in a 30ml universal container in the field and then transported to the laboratory in Blantyre in a cold box at 4–8°C. Subsequently the sample was enriched in selenite broth and incubated overnight at 37°C before aliquoting and freezing at -70°C. Bacterial DNA extraction on the stored selenite samples will be done in batches within 14 days of collection. To avoid any age-related bias, batched analysis will be performed in the order in which the samples were collected. DNA will be extracted from pure cultures using the Omega BioTek Mag-Bind Universal Pathogen kit on the Thermo KingFisher Flex, and then sequenced using Illumina sequencing according to the manufacturer’s instructions.

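### The power for the eNTS effect on SBA assumes an SD of 0.4, but four other SBA rows of Table 4 imply an SD of about 1.6, so the column is not on one basis

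*Protocol article*

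**What the plan says.** Protocol article, Sample size, Change in SBA due to eNTS. The calculation starts "With a sample size of 2,500 recruited individuals, 20% loss to follow-up". The target is "a difference of 0.2 in SBA between children with salmonella PCR-positive stools compared to those with negative stools", and the result is that it "can be detected in the three-month follow-up visit sample with 99.97% power, assuming a standard deviation of 0.4 for SBA". The Figure 6B caption supplies the exposed share: "Power for detecting change in SBA following enteric salmonella exposure (8%) prevalence (N=2500".

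Table 4 puts this result in the column headed "Difference in SBA between 3 monthly samples (CFU/ml"), with power given as both at least 80% and 99.97%. The same column lists malaria (16% prevalence, 0.25), moderate to severe anaemia (20%, 0.225), malnutrition (2%, 0.65), sickle cell disease (1%, 0.9) and RTS,S vaccination (60% coverage, 1.5), each with power of at least 80%.

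Changes in serum bactericidal activity by age ties the malaria row to 2,500 paired samples, which are called "well-powered (power >80%) to detect changes in SBA of 0.25 CFU/ml between three-monthly samples". The article states no SD for any SBA row except eNTS.

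**The concern.** Table 4 invites the reader to compare detectable SBA differences across risk factors in one cohort. The comparison fails on sight. The eNTS row has fewer exposed children than the anaemia row (8% against 20%) and a smaller target (0.2 against 0.225), yet its power is 99.97% where anaemia is given at the 80% mark. With a common SD and a common method that ordering is impossible.

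SBA is one of the two primary measures of immunity in Statistics and analysis. Modelling the effect of eNTS at visit 1 on immunity at visit 2 is a stated purpose of the stool testing. Whether power for 0.2 is near certainty or nearer one in three decides whether a null eNTS result would be informative. In the other direction, if 0.4 is the right SD, the article understates fourfold how small an effect of malaria or anaemia it can detect.

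**Working it through.** **Inputs.** Differences and prevalences come from Table 4. The SD of 0.4, the 2,500 recruited and the 20% loss come from Change in SBA due to eNTS. Significance level and sidedness are not stated, so two-sided 5% is assumed. Normal approximation for two unequal groups:

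- s = √(1/(Np) + 1/(N(1−p)))
- power = Φ(d/(SD·s) − 1.96)
- implied SD at 80% power = d/(2.80·s)

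**1. The plan's own figure.** 2,500 less 20% is 2,000 children, 160 exposed and 1,840 not. s = √(1/160 + 1/1840) = 0.0824. d/(SD·s) = 0.2/(0.4 × 0.0824) = 6.07. Power = Φ(4.11) = 99.998%. The printed 99.97% is slightly lower (1,600 pairs would give 99.974%), but the difference is immaterial. The figure follows from its stated SD.

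**2. SD implied by the other SBA rows.**

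| Row | p | d | s (N=2,500) | SD, 2,500 pairs | SD, 2,000 pairs |
|---|---|---|---|---|---|
| Malaria | 16% | 0.25 | 0.0546 | 1.64 | 1.46 |
| Anaemia | 20% | 0.225 | 0.0500 | 1.61 | 1.44 |
| Malnutrition | 2% | 0.65 | 0.1429 | 1.62 | 1.45 |
| Sickle cell disease | 1% | 0.9 | 0.2010 | 1.60 | 1.43 |
| RTS,S | 60% | 1.5 | 0.0408 | 13.1 | 11.7 |

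The first four agree within about 2% over a 20-fold range of prevalence, which points to one common effective SD. The RTS,S row does not belong with them and must have been computed in another way.

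At 90% instead of 80% power, the four values at 2,500 pairs would be 1.38 to 1.41, still more than three times 0.4. For its own 0.2 to reach 80% power, the eNTS row needs an SD of at most 0.97 (2,500 pairs) or 0.87 (2,000).

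**3. Level or change.** The eNTS text refers to the follow-up sample, while the other rows refer to change between samples. If one value has SD 0.4 at each visit, a change has SD 0.4·√(2(1−ρ)). That is 0.57 at ρ = 0 and 0.8 at the extreme ρ = −1. Neither reaches 1.45.

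**4. If the other rows' SD applies to eNTS (d = 0.2, p = 8%).**

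| SD | Pairs | Power | 80%-detectable difference |
|---|---|---|---|
| 1.6 | 2,500 | 39.6% | 0.33 |
| 1.6 | 2,250 | 36.3% | 0.35 |
| 1.6 | 2,000 | 32.9% | 0.37 |
| 1.45 | 2,000 | 39% | 0.33 |

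The 2,250 line reflects the 10% drop-out that Study design gives for the power calculations. The lowest figure pairs an SD derived at 2,500 with 2,000 analysed. The matched pairings (1.6 at 2,500; 1.45 at 2,000) both give 39–40%.

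**5. If 0.4 applies to all (N = 2,500).** The 80%-detectable differences, 2.80 × 0.4 × s, are malaria 0.061, anaemia 0.056, malnutrition 0.16 and sickle cell disease 0.225, each about a quarter of the printed value.

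**The case against.** The strongest reply is that 1.6 appears nowhere in the article. It rests on a plain two-group test at exactly 80% power, whereas the rows say at least 80%, so it is strictly an upper bound. The same inversion gives no common SD in the antibody column (85, 93, 117 and 121 for the same four risk factors) and about 13 for RTS,S, so Table 4 may not rest on such a test. The 20-per-arm longitudinal calculation implies about 0.85 if read as a single-visit comparison, although it uses repeated visits.

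The SBA simulations are also described as by age. A model with an exposure-by-age interaction and uncentred age enlarges the standard error of the exposure term: by about 2 with linear age and about 3 with quadratic age, for ages spread uniformly over 0–60 months. Combined with √2 for a change score, 0.4 becomes about 1.1 to 1.7. The code is cited but not shown, so this cannot be excluded.

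These points stand against calling 1.6 the SD of SBA. They do not reconcile the column. If the other rows used a different model, the eNTS power was still computed on another basis and the article does not say so.

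A reader might go further in three ways that the documents do not support.

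- That 99.97% is a miscalculation. It approximately reproduces under its stated SD.
- That true eNTS power is 33%. That depends on an inferred SD, and Figure 6B, said to cover a range of assumptions, is not available here.
- That malnutrition and sickle cell disease were made exploratory on a wrong SBA figure. Changes in antibody titer by age bases that status on titre differences of 47 and 68, described as "which is much less sensitive than the other methods". The SBA SD does not affect these.

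**Conclusion.** The point holds as an inconsistency of basis within the SBA column of Table 4. The eNTS power uses an SD of 0.4. Four other rows behave as if the effective SD were about 1.6 (about 1.45 after 20% loss), and the RTS,S row fits neither. The level-to-change distinction alone does not explain a gap of this size.

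As printed, the column cannot show which SBA effects the cohort can detect. Depending on which basis is right, either eNTS power for 0.2 is about 33–40% with a detectable difference of 0.33–0.37, or the four other detectable differences are about four times too large. The documents do not settle which. The sizes assume a two-sided 5% level, a two-group comparison and rows set at the 80% threshold. Nothing here shows that the sample size itself is inadequate.

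**What to change.** Re-run every SBA row of Table 4 with the existing simulation code, using:

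- one justified SBA SD;
- the scale of the planned assay, since the table is labelled CFU/ml while Sample storage and analysis describes a luminescent readout "without the need for overnight incubation or colony counting";
- the same number of pairs after loss;
- the same model, saying whether the outcome is the follow-up level or the change.

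State these, with the significance level, for each row, and explain or correct the RTS,S row. Then replace the 99.97%, the other rows' differences, or both with the reconciled results. If a row needs a different SD or model, say so and give the reason. The back-calculated values above should not be printed as the study's own assumptions.

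The cost is one re-run and a corrected table and paragraph. No extra children, samples or visits are needed. The downside is that a stated power may become less favourable.
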